### The intervention

#### General outline

The intervention is based on the stages of change and organizational change theories and tailored by formative research [25-27]. Opinion leaders in the 12 intervention hospitals will be identified by their peers through a specific questionnaire and trained in a five day workshop to develop and implement evidence-based guidelines. They will then use a specified multifaceted approach to disseminate, implement, and maintain the guidelines in their hospitals. The 18-month intervention will include training to perform the evidence-based best practices, use of a web site, academic detailing, reminders, and feedback on utilization rates. Those components which will form the intervention are noted in Table 1 and are described in detail below.

**Table 1 T1:** Components of the intervention

**Selection of opinion leaders**
- Teams of 3–6 birth attendants per hospital
- Selected by peer nomination
**Interactive workshops**
- Opinion leaders teams will participate in a 5 day workshop
- Objectives:
- To learn the need of an evidence based clinical practice
- To develop simple evidence based guidelines about episiotomy use and management of the third stage of labor
- To identify the barriers for the adoption of those guidelines at the hospital level
- To learn how to overcome barriers and to implement the guidelines
- To adapt and organize the dissemination and implementation of the guidelines in their hospitals
**Academic detailing**
- Dissemination of the guidelines to hospital birth attendants in small groups and individual discussions
- Identification of barriers to implement the guidelines
- Adaptation and organization of implementation activities working closely with birth attendants.
**Training on how to comply with the recommended practices**
- Training in manual abilities with videos, anatomical models and patients. One day workshop.
**Reminders**
- Placing reminders of selective episiotomy and active management of the third stage of labor in labor and delivery wards, clinical records, and surgical packages.
**Audit & feed back**
- Monthly reports of hospital episiotomy and active management rates to be distributed to every birth attendant.
**Information technology**
- Each hospital in the intervention group will receive a computer with internet access
- A specific web site will be developed to facilitate the access to study manuals and guidelines, sources of evidence-based health care literature (Reproductive Health Library, Cochrane Library), and communication among hospitals and study coordinators

#### Formative research

With the aim of refining the intervention strategy and better integrating the intervention into the hospitals' routine, a qualitative study was carried out during the preparatory phase of the trial. We conducted three in-depth interviews with upper level physician administrators (responsible for the clinical and administrative management of the departments), three focus groups with second level physicians (responsible for the individual provision of clinical care to users) and three focus groups with midwives. Additionally we conducted three focus groups with pregnant women to explore their perspectives regarding the health care they receive and their expectations of the birth practices routinely used.

#### Selection of opinion leaders

Each intervention hospital will select a team of opinion leaders who will work collaboratively during the intervention period. Each team will be composed by three to six professionals per hospital, with representation by obstetricians, residents and midwives. The department chair will be invited to designate one professional not included in the nominated team. Peer nomination will identify opinion leader team members among the professional staff of the maternity hospital using a previously validated sociometric questionnaire [28].

#### Guideline development and implementation workshops

All opinion leader teams will participate in a regional five-day workshop. There the teams will learn about the scientific basis for evidence based clinical practice, they will develop simple evidence based guidelines for episiotomy use and for the management of the third stage of labor. They will additionally suggest the main barriers for the implementation of those guidelines, and will learn and practice ways to overcome such barriers in the context of the planned intervention. Finally, each team will adapt the planned guideline dissemination and implementation activities to the characteristics of their own hospital, and will develop an organizational approach directed at the interventions.

The workshops will be given in five consecutive days, in a selected site outside the hospital walls, and will be conducted by trainers with previous experience in conducting related workshops in Latin American countries that will act as tutors, together with the country coordinators. Each tutor will guide a group with no more than 10 participants.

#### Web portal

Each hospital in the intervention group will receive a computer, access to the internet, the last issue of the WHO Reproductive Health Library [29] and access to the Cochrane Library in Spanish [30]. A study web site will be developed to facilitate the easy access to guidelines, workshop manuals, medical literature and electronic libraries and databases. This tool will be presented to the teams during the workshops, and they will later introduce the portal to each intervention hospital staff as part of the dissemination activities. The portal will be for the exclusive use of the professional staff at the intervention hospitals. A password access system will be in place during the intervention.

#### Training on manual skills

After completion of training, each opinion leader team will participate in a one-day workshop on clinical management skills (how to assist a delivery without episiotomy, and active management of the third stage of labor) using videos, anatomical models, and patients, conducted by the country coordinator or a trainer with previous experience. This workshop is based on the JHPIEGO workshop [31] currently being organized in several Latin American countries.

#### Dissemination of guidelines at the hospital and identification of barriers

Each opinion leader team disseminates the guidelines among the professional staff at its respective hospitals. They will primarily utilize academic detailing as the strategy for this purpose [32]. The team will present and discuss the guidelines with all birth attendants, providing to each one the opportunity to discuss them and to identify specific barriers; the birth attendants will adapt the planned activities for overcoming the barriers and develop an implementation timetable. Finally, the team will present the web portal, and will select a group of potential early adopters (volunteers) who appear enthusiastic for participation in the implementation of the guidelines.

#### Implementation and maintenance of guidelines

The objective of this component is to facilitate deliveries by birth attendants according to the recommendations developed in the workshops. Three strategies will be carried out to achieve this aim:

a) Training on how to do the recommended practices: all birth attendants will receive one training session given by the opinion leaders, on anatomical models and on patients.

*b*) Placing reminders: there will be short messages that remind birth attendants to consider the two evidence-based birth practices of interest:

• Active management reminders: to be placed in the partograph and as posters in the delivery ward.

• Selective episiotomy reminders: to be placed on the surgical package for assisting delivery and in the partograph.

The text of the reminders will be prepared by the opinion leader teams according to the designed recommendation and will take into account the characteristics and barriers of each specific hospital.

c) Monthly reporting of the episiotomy rates and the use of oxytocin for management of the third stage of labor at the hospital level: This information will be produced by their Perinatal Information System (PIS) [33] and distributed to birth attendants.

The intervention will be pilot tested in two hospitals similar to the hospitals that will participate in the trial.

### Activities in control hospitals

Birth attendants from hospitals in the control group will receive no intervention after randomization other than their standard in-service training activities and standard sources of information. We intend to provide birth attendants with the guideline development component, a computer and bibliography *following *the completion of the study.

### Outcome measures

The primary outcomes are aimed at changing the birth attendants' behavior relative to the rate of episiotomy and the rate of injection use of 10 I.U. of oxytocin during third stage of labor. Secondary clinical outcomes will be studied to estimate the health impact of the intervention, including the rate of perineal sutures use and the incidence of postpartum hemorrhage >500 ml. These outcomes will be assessed in singleton vaginal deliveries. We will also measure the provider's readiness to change with respect to episiotomies and management of third stage of labor with a specific questionnaire.

All outcomes will be assessed for a three-month period at three time points: at baseline (before randomization), after the end of the intervention, and the primary outcomes one year after the end of the intervention to measure the long term effects of the intervention. Interim analysis will be performed as required by the Data and Safety Monitoring Committee.

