**Methods/Design:**

The aim of this trial is to evaluate the effect of a multifaceted behavioral intervention on the use of two evidence-based birth practices, the selective use of episiotomies and active management of the third stage of labor (injection of 10 International Units of oxytocin). The intervention is based on behavioral and organizational change theories and was based on formative research. Twenty-four hospitals in three urban districts of Argentina and Uruguay will be randomized. Opinion leaders in the 12 intervention hospitals will be identified and trained to develop and implement evidence-based guidelines. They will then disseminate the guidelines using a multifaceted approach including academic detailing, reminders, and feedback on utilization rates. The 12 hospitals in the control group will continue with their standard in-service training activities. The main outcomes to be assessed are the rates of episiotomy and oxytocin use during the third stage of labor. Secondary outcomes will be perineal sutures, postpartum hemorrhages, and birth attendants' opinions.

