Our hypothesis is that a multifaceted intervention designed to increase birth attendant concern about the effectiveness of routinely used birth practices, to provide them with resources and skills to access, interpret, and develop evidence-based clinical guidelines, and to establish mechanisms facilitated through key hospital leaders, to implement the guidelines and sustain them over time, will increase the use of evidence-based birth practices in Latin American hospitals. The primary objective of this trial is to evaluate the effect of this multifaceted behavioral intervention on the use of two evidence-based birth practices, the selective use of episiotomies and active management of the third stage of labor (injection of 10 IU of oxytocin). Secondary objectives are to evaluate the effect of the intervention on rates of post-partum hemorrhage, use of perineal sutures and to document readiness to change among birth attendants.

Additionally, through this process we intend to improve the research capacities of a network of Latin American hospitals, and thus increase their ability to perform quality local and collaborative research studies.

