### Data collection

Although the hospital will be the unit of analysis, we shall collect individual patient data in order to assure data quality. The goal is to accumulate data on approximately 300–500 deliveries from each hospital. All the hospitals in the project use a standard perinatal clinical record form (PIS form) [33]. This form includes the data of the obstetric history, prenatal care, labor, delivery, and neonatal outcomes. To obtain the additional necessary data to calculate the outcome variables, we will implement a modified version of the PIS clinical record that will add some variables at the bottom of the form to be addressed during the data collection periods. This approach will reduce to a minimum extra activities associated with data collection by the birth attendants during the study.

Blood loss during the third stage of labor (after delivery) will be measured from all vaginal deliveries during the data collection periods. A plastic, transparent, collection drape will be employed. At the end of the blood collection period, the amount of blood loss will be measured by pouring the contents of the drape into a calibrated pitcher. The amount of blood loss will be recorded in the data form together with the time (beginning and end) of the blood collection.

To measure provider's readiness to change, a self-administered questionnaire was designed and will be completed by all physicians and midwives at all participating hospitals, before randomization and at the end of the intervention.

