### Sample size

The sample size was estimated based upon the hospital being the unit of analysis. A preliminary analysis of data from Argentinean hospitals [2] documented a baseline frequency of episiotomies in vaginal deliveries of 42%, with a standard deviation of 11%. To protect against changes in the standard deviation [15], we have based our calculations on a standard deviation of 15%. Thus, we need 18 hospitals (9 intervention and 9 control) to identify a decrease of episiotomy rates from 40% to 20%, with a 0.05 significance level and 80% power. Considering that in public hospitals in Argentina and Uruguay about 25% of deliveries are seen among primiparae, and 75% among multiparae, a reduction of the general episiotomy rate from 40% to 20% could be achieved by reducing the rate among primiparae from 80% to 40%, and the rate among multiparae from 26% to 13%. The rates after this intervention would thus be similar to the rates achieved in a previous trial [34] and are therefore potentially attainable. Moreover, the sample size of 18 hospitals will allow identification of smaller decreases of episiotomy rates among primiparae vaginal deliveries, from 80% to 60%, with a 0.05 significance level and 80% power.

We expect the use of oxytocin during the third stage of labor to increase from 10% to 50%. However, assuming a baseline frequency of oxytocin use of 10% and a standard deviation of 5%, a sample size of 18 hospitals will provide a power > 95% to identify an increase in oxytocin use from 10% to 20%, with a 0.05 significance level. Assuming a baseline incidence rate of post-partum hemorrhage of 15% and a standard deviation of 5%, a sample size of 18 hospitals will provide a power of 84% to identify a reduction in hemorrhage from 15% to 8%.

Hospitals will initiate baseline data collection to obtain information that will be used to assess the inclusion criteria before randomization. A total of 24 hospitals were included to allow for hospital drop-outs.

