### Ethical aspects

This is a cluster randomized trial with an intervention targeted at the cluster (hospital) level; the behavioral intervention will be directed to the entire group of birth attendants at each intervention hospital. Given that the purpose of the study is to improve the quality of care at the hospitals, this should not imply any additional risk for women and their children. Birth attendants are the subjects of the trial, although the main outcomes will be measured in terms of the patient. All responsible hospital authorities are to be provided written agreements to participate in advance of randomization [37,38]. Birth attendants in the intervention hospitals will receive a fact sheet with information as to the format, length, and purpose of the training intervention. In addition, birth attendants who are nominated as opinion leaders in the intervention hospitals will also provide written agreements to participate in that role.

The necessary data for outcome measurement is routinely collected at the hospitals, and no personal identifiers will be transmitted with in the data to the coordinating unit; thus there will be need no need to obtain informed consent from patients.

All birth attendants will provide written consent before filling out the 'Readiness to Change' questionnaire and all measures will be taken to keep their identities confidential

The protocol was submitted and approved by the IRBs of the following institutions: University of North Carolina at Chapel Hill; Tulane University; Research Triangle Institute; Pan American Health Organization; School of Medicine of the University of the Republic in Uruguay; the University Hospital of Montevideo, Uruguay; and the Argentinean Society for Clinical Research.

The trial is registered at the NIH clinical trials register (; Identifier: .NCT00070720) and at the Current Controlled Trials Register ; ISRCTN82417627).

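### The any-suture rate, the only perineal outcome named to estimate health impact, largely follows the episiotomy rate if episiotomies are sutured, and read alone it can suggest benefit while tears increase

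*Protocol article*

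**What the plan says.** The protocol article lists the secondary outcomes in three places, and the lists agree.

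- Outcome measures: "Secondary clinical outcomes will be studied to estimate the health impact of the intervention, including the rate of perineal sutures use". The only other clinical outcome named is postpartum hemorrhage above 500 ml. On the denominator: "These outcomes will be assessed in singleton vaginal deliveries".
- Abstract, Methods/Design: "Secondary outcomes will be perineal sutures, postpartum hemorrhages, and birth attendants' opinions".
- Secondary objectives, at the end of the Background: to "evaluate the effect of the intervention on rates of post-partum hemorrhage, use of perineal sutures and to document readiness to change among birth attendants".

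None of these names spontaneous tears, tear grade, or sutures in women without episiotomy.

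Three other statements bear on the point. Sample size sets the planned effect: "we need 18 hospitals (9 intervention and 9 control) to identify a decrease of episiotomy rates from 40% to 20" per cent. Ethical aspects says of the trial that "this should not imply any additional risk for women and their children". Data collection says that individual patient data are gathered, and that the modified perinatal record will "add some variables at the bottom of the form to be addressed during the data collection periods". Those variables are not listed.

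**The concern.** The intervention aims to halve the use of one perineal procedure. The perineal health question that follows is whether spontaneous tears become more frequent or more severe in the women who are spared it. The plan's perineal measure of health impact is a rate of any suture. If an episiotomy is ordinarily repaired, each one counts as a suture, so the secondary outcome contains the primary one. A fall in sutures may then largely restate the behavioral result. The measure also scores a minor tear repair, an episiotomy repair and a severe tear repair alike, and a tear left unsutured is not counted.

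At stake is the interpretation. A reader given the suture rate as evidence of health impact could take its fall as a clinical gain additional to the fall in episiotomy, while tears had in fact increased.

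**Working it through.** **The plan's own figure.** Sample size states "we have based our calculations on a standard deviation of 15" per cent for the between-hospital spread and a 20-point difference, at a 0.05 level and 80% power. By the normal approximation, two-sided, n per arm = 2 × (1.960 + 0.842)² × 0.15² / 0.20² = 8.83, rounded up to 9, or 18 hospitals. This reproduces the stated number. It is context only: the article gives no figure for sutures or tears, and nothing below depends on power.

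**Inputs.**
- Episiotomy rate E: 40% before and 20% after (Sample size).
- Every episiotomy is sutured: assumption, not stated in the article.
- t, the share of women without episiotomy who have a sutured tear: not given. Assumed 20% to 40%, with 5% to 50% as a wider range.

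**Formulas.**
- Suture rate: S = E + (1 − E) × t
- Sutured tears without episiotomy, over all births: T = (1 − E) × t = S − E
- Value of t after the intervention at which S stops falling: (0.40 + 0.60t − 0.20) / 0.80 = 0.25 + 0.75t

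**Results with t unchanged.**

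| t | S before → after | Change in S (points) | T per 100 births | S stops falling at t = |
|---|---|---|---|---|
| 5% | 43% → 24% | −19 | 3 → 4 | 28.8% |
| 10% | 46% → 28% | −18 | 6 → 8 | 32.5% |
| 20% | 52% → 36% | −16 | 12 → 16 | 40% |
| 30% | 58% → 44% | −14 | 18 → 24 | 47.5% |
| 40% | 64% → 52% | −12 | 24 → 32 | 55% |
| 50% | 70% → 60% | −10 | 30 → 40 | 62.5% |

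For t = 20%: before, 0.40 + 0.60 × 0.20 = 0.52; after, 0.20 + 0.80 × 0.20 = 0.36. T rises by one third in every row because the share of women without episiotomy goes from 60% to 80%.

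**A check that does not hold t fixed.** Let r be the share of the 20 women per 100 spared an episiotomy who instead have a sutured tear, with nothing else changed. Then S changes by −20 × (1 − r) points and T by +20 × r. At r = 50%, sutures fall by 10 points while sutured tears rise by 10. At r = 100%, S does not change.

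**Severity.** Suppose severe tears went from 1% to 2% of births (assumed). S would rise by at most 1 point on that account, even if all the extra cases would otherwise have had no suture. That compares with a fall of 12 to 16 points from the episiotomy change. At the 300 to 500 deliveries per hospital given under Data collection, 1% is 3 to 5 cases per hospital.

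**The case against.** The strongest reply is that the suture rate answers a fair question: does less episiotomy mean less perineal repair overall, or are cuts replaced by sutured tears? It is a legitimate measure of total repair. A reader might infer that it falls mechanically and cannot show whether tears increased. The documents do not support that. The fall is net, and it disappears at r = 100% or at the values in the last column of the table. A suture rate that failed to fall would itself signal more sutured tears. Episiotomy and suture are both planned outcomes on the same deliveries, with individual data, so S − E can be derived. At t = 20% it shows the rise from 12 to 16. If t reached 40%, S would stay at 52% but S − E would go from 12 to 32.

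Three other strong readings also fail:
- Nothing in the trial could contradict the statement about risk in Ethical aspects. Hemorrhage is measured, by collection drape, and a suture rate that did not fall would count against it too.
- The plan will present a fall in sutures as independent of the behavior change. The article says only that health impact is to be estimated.
- The form holds one undifferentiated suture item. The article does not describe the item, and the form may already record tears.

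It can also be said that the article condenses a fuller protocol, that its Outcome measures section introduces the list with an open word, and that the trial tests uptake of practices it treats as established. These points weaken the concern without removing it. The abstract and the objectives give the same list, neither mentions tears, and S − E is derivable but is not a specified outcome. Even if reported, it would not show severity, unsutured tears or extensions of an episiotomy.

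**Conclusion.** The concern stands in limited form. As named in the article, the only perineal outcome meant to estimate health impact largely follows the primary outcome. At the planned effect it falls by 12 to 16 points for t between 40% and 20% (10 to 19 points over the wider range of 50% to 5%), while sutured tears over all births rise by one third. This rests on two assumptions that the article does not supply: that episiotomies are sutured, and that t is unchanged. The r calculation relaxes the second and still allows sutures to fall while sutured tears rise.

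What the rate misses even when read beside the episiotomy rate is severity and unsutured tears. The fault is reliance on it as the sole perineal measure, not its inclusion.

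**What to change.** 1. Keep the any-suture rate as a secondary outcome, described as total perineal repair.
2. Specify suture without episiotomy, per singleton vaginal delivery, as a separate secondary outcome. It can be derived from the individual data already planned and needs no new collection.
3. If the modified record does not already capture it, add one coded item for third- or fourth-degree tear, with or without episiotomy. Report it by arm as a descriptive safety outcome.
4. State that a fall in the any-suture rate will not be interpreted as a health effect separate from the fall in episiotomy.

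Items 1, 2 and 4 cost only wording. Item 3 costs one field on a form already being changed, and it has limits. Severe tears are expected to be rare, so the estimate will be imprecise. The attendants who grade tears know their hospital's allocation. Because baseline data have already been collected, a new item may have no baseline value, which leaves a comparison between arms after the intervention only.
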